### Statistical analysis

2.13

All analyses will follow a pre-specified hierarchical statistical analysis plan finalised prior to database lock to minimise the risk of data-driven inference.

#### Primary analysis

2.13.1

The primary outcome, defined as the correlation between Anti-Xa activity (UFH/LMWH) and CT in the RVV-assay. Because two measurements per patient are planned, the primary inferential analysis will be conducted using a linear mixed-effects model including:

A random intercept for patientA fixed effect for anticoagulant type (UFH vs. LMWH)

This approach accounts for intra-individual correlation and avoids inflation of type I error due to non-independence of repeated observations. Results will be reported as regression slope estimates (per 0.1 IU/mL increase in Anti-Xa activity) with 95% confidence intervals. For descriptive comparability with previous literature, Spearman rank correlation coefficients with bootstrap-derived 95% confidence intervals will additionally be reported:

For the overall cohortStratified by anticoagulant type

Passing–Bablok regression will be applied as a robust method-comparison technique to assess proportional and systematic bias between CT-RVV and Anti-Xa activity (36). Proportional bias will be considered absent if the 95% confidence interval (CI) of the slope includes 1.0, and constant bias absent if the 95% CI of the intercept includes 0.

These criteria are used for methodological characterization rather than to demonstrate assay equivalence. The primary objective is not interchangeability but to determine whether CT-RVV exhibits a stable monotonic relationship with Anti-Xa activity under ICU conditions.

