### Sample size

2.12

This study is designed to evaluate the association between Anti-Xa activity and VET variables, with a primary focus on CT in the RVV test, in critically ill patients receiving LMWH or UFH. The planned sample size allows estimation of this association under real-world ICU conditions and supports pre-specified mixed-effects modelling incorporating a limited number of biologically plausible effect modifiers. To account for heterogeneity in coagulation physiology, anticoagulant type (LMWH vs. UFH) and sepsis status will be examined as predefined effect modifiers within the modelling framework. These factors will not be treated as independently powered subgroups but will be analysed using interaction terms. The study is not powered for definitive detection of small correlation coefficients nor for confirmatory subgroup comparisons. Stratified analyses are therefore considered exploratory and hypothesis-generating. Findings will be interpreted cautiously and are intended to inform the design of future adequately powered multicentre studies.

The study is powered for estimation of the Anti-Xa–CT association. Analyses involving thrombin generation are predefined as secondary and exploratory. No separate formal sample size calculation was performed for TGA-CT correlations, as these analyses are hypothesis-generating. The sample size estimation was based on published data reporting a significant Spearman correlation for LMWH-treated patients between Anti-Xa levels and CT-RVV (*r* = 0.669, *p* = 0.0395) (34). For UFH, no exact coefficient was reported, although the same study demonstrated a clear association. For conservative planning, an effect size of *r* = 0.6 was assumed for UFH.

Calculations were performed with G*Power 3.1 (35) for a two-sided test of correlation (*α* = 0.05, power = 0.80). The required sample sizes were 19 independent observation pairs for *r* = 0.669 and 23 pairs for *r* = 0.6. As two temporally separated measurements are planned per patient, the non-independence of repeated measures was adjusted using a design effect with an intraclass correlation coefficient (ICC) of 0.3:

Design−Effect=1+(2−1)×0.3=1.3

$$\text{Effective observations}\;\mathrm{per}\;\text{patient}=\frac{2}{1.3}\approx 1.54$$

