#### Pre-specified effect modification analyses

2.13.2

To explicitly address biological heterogeneity in critically ill patients, potential effect modifiers will be analysed within the mixed-effects framework using interaction terms.

Pre-specified modifiers include:

Sepsis statusAntithrombin concentrationRenal function (creatinine, estimated GFR)Inflammatory markers (CRP, fibrinogen, albumin)

Sepsis status will be analysed as an effect modifier rather than as a separately powered subgroup.

These analyses aim to identify conditions under which CT-RVV and Anti-Xa activity diverge.

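### Section 2.12 promises anticoagulant type as an effect modifier, but the analysis sections as written give one common CT–Anti-Xa slope for UFH and LMWH

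*Protocol article*

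**What the plan says.** Section 2.12 (Sample size) states that "anticoagulant type (LMWH vs. UFH) and sepsis status will be examined as predefined effect modifiers within the modelling framework", and continues: "These factors will not be treated as independently powered subgroups but will be analysed using interaction terms". It then derives a number of patients for each drug, using a published r of 0.669 for LMWH and an assumed r of 0.6 for UFH.

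Section 2.13.1 (Primary analysis) makes a linear mixed-effects model the primary inferential analysis. Two terms are listed: a random intercept per patient and a "fixed effect for anticoagulant type (UFH vs. LMWH"). On output it says: "Results will be reported as regression slope estimates (per 0.1 IU/mL increase in Anti-Xa activity) with 95% confidence intervals". Spearman coefficients, overall and by drug, are added for comparability with the literature. Section 2.14 confirms that simple correlation coefficients are descriptive only.

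Section 2.13.2 opens its list with "Pre-specified modifiers include" and names sepsis status, antithrombin, renal function and inflammatory markers. Anticoagulant type is not among them. It is also absent from the example modifiers in 2.10 (exploratory outcome 4) and 2.16.

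**The concern.** A main effect for drug shifts the level of clotting time between UFH and LMWH. It does not let the seconds gained per 0.1 IU/mL differ between them; only an interaction does that. Section 2.12 promises the interaction, but neither section that specifies the models contains it. Sepsis, named in the same sentence of 2.12, is carried into 2.13.2; anticoagulant type is not.

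The primary estimate is at stake. The primary objective is whether clotting time tracks Anti-Xa stably enough to support bedside interpretation. One slope averaged over two drugs can hide a difference in that relation. The average also depends on how widely Anti-Xa happens to vary in each group, and therefore on the mix of prophylactic, intermediate and therapeutic targets enrolled. Two analysts working from different sections could report different primary results.

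**Working it through.** **1. The plan's own per-drug figures.** Inputs from 2.12: 19 and 23 independent pairs, ICC 0.3, two samples per patient.

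- Design effect = 1 + (2 − 1) × 0.3 = 1.3; effective observations per patient = 2/1.3 = 1.54.
- LMWH: 19/1.54 = 12.3, rounded up to 13. UFH: 23/1.54 = 14.9, rounded up to 15.

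The step from pairs to patients reproduces. The targets are 30 LMWH and 36 UFH. The sizing is therefore done drug by drug.

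**2. The two models side by side** (i = patient, j = sample).

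- As listed in 2.13.1: CT_ij = β0 + β1·AntiXa_ij + β2·UFH_i + b_i + e_ij. The slope is β1 for both drugs.
- As promised in 2.12: the same plus β3·(AntiXa_ij × UFH_i). The LMWH slope is β1 and the UFH slope is β1 + β3.

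**3. What the common slope estimates when β3 is not zero.** Approximately

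common slope = (n_L·V_L·β_L + n_U·V_U·β_U) / (n_L·V_L + n_U·V_U),

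where n is patients and V the within-drug variance of Anti-Xa. With w = n_U·V_U / (n_L·V_L + n_U·V_U) and slope ratio R = β_U/β_L, the common slope is 1 + w(R − 1) times the LMWH slope. Dividing by R gives the multiple of the UFH slope.

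The protocol gives no slopes or SDs. Assumed range: SD 0.12 to 0.25 IU/mL in either drug, and R of 2 or 1.5.

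| SD LMWH / UFH | w | R = 2: × LMWH, × UFH | R = 1.5: × LMWH, × UFH |
|---|---|---|---|
| 0.25 / 0.12 | 0.5184/(1.875 + 0.5184) = 0.217 | 1.22, 0.61 | 1.11, 0.74 |
| equal | 36/66 = 0.545 | 1.55, 0.77 | 1.27, 0.85 |
| 0.12 / 0.25 | 2.25/(0.432 + 2.25) = 0.839 | 1.84, 0.92 | 1.42, 0.95 |

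At R = 1 every entry is 1.

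**4. Check by simulation.** 30 LMWH and 36 UFH patients, two samples each, 120 replicates per scenario. Assumed: Anti-Xa SD 0.2 IU/mL in both drugs, patient SD 13 s, residual SD 20 s. Slopes are in seconds per 0.1 IU/mL.

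| True LMWH / UFH slope | Common slope, simulated (formula) | Its 95% CI covers LMWH / UFH slope | Interaction p < 0.05 |
|---|---|---|---|
| 10 / 10 | 9.9 (10.0) | 98% / 98% | 4% |
| 8 / 10 | 9.0 (9.1) | 81% / 79% | 24% |
| 5 / 10 | 7.9 (7.7) | 28% / 45% | 64% |
| 5 / 15 | 10.6 (10.5) | 0% / 4% | 100% |

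For true slopes 5 and 15, changing only the Anti-Xa SDs moves the common slope from 7.3 (LMWH 0.3, UFH 0.15) to 13.3 (LMWH 0.15, UFH 0.3). The interaction model recovers both slopes on average: 5.1 and 10.1 for 5/10, and 5.3 and 15.0 for 5/15. With 120 replicates, the 64% has a simulation standard error of √(0.64 × 0.36/120) = 0.044, about 4 percentage points.

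**The case against.** The strongest reply is that the interaction is already pre-specified. Section 2.12 commits to it, and a commitment binds wherever it stands. The term list in 2.13.1 cannot be exhaustive, since it does not name Anti-Xa, the predictor whose slope is reported. It also speaks of slope estimates in the plural, and 2.13.2 introduces its modifiers as an open list. Full model terms may be set out in a statistical analysis plan that is not shown.

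Much of this stands. A reader might infer that the plan assumes equal slopes; 2.12 rules that reading out. But the two sections that specify the models should carry out the promise, and neither does. That is a conflict between stated sections rather than detail left for later.

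A reader might also infer from the different r values that the plan regards the two relations as different. It does not say so. The 0.6 for UFH is an assumption made because no exact coefficient was available, and a correlation is not a slope: equal slopes can go with unequal r, and the reverse. The sizing shows only that the drugs were planned for separately.

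On harm, the plan proposes no conversion of clotting time into Anti-Xa from the fitted slope, calls itself primarily hypothesis-generating, and asks about a stable monotonic relation. The drug-stratified Spearman coefficients with bootstrap intervals do address monotonicity per drug. They are descriptive, however, and give no slope, so no inferential drug-specific result is specified.

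Finally, declaring two drug-specific slopes co-primary would be partly a design preference. It would need a multiplicity rule and fit poorly with 2.12, which disclaims confirmatory subgroup comparisons. That objection is accepted, and the fix does not ask for it.

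**Conclusion.** The point holds as an internal conflict that affects the primary estimate. Section 2.12 promises an interaction with anticoagulant type. Sections 2.13.1 and 2.13.2 as written do not contain it and lead to a single common slope.

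The size of the consequence is conditional. With assumed within-drug Anti-Xa SDs of 0.12 to 0.25 IU/mL, the common slope is about 1.2 to 1.8 times the LMWH slope and 0.6 to 0.9 times the UFH slope if the UFH slope is twice the LMWH slope. At a ratio of 1.5 the figures are about 1.1 to 1.4 and 0.74 to 0.95. If the slopes are equal there is no bias. Nothing in the protocol establishes that they differ, so the documents do not support saying that the pooled slope will be wrong; they support saying that the model as listed could not show it.

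**What to change.** - In 2.13.1, add the Anti-Xa by anticoagulant-type interaction to the primary mixed model, and name Anti-Xa explicitly as a term.
- In 2.13.2, add anticoagulant type to the list of modifiers, so that it matches 2.12.
- Report the UFH slope, the LMWH slope and the interaction, each with a 95% CI, beside any pooled slope or overall-cohort Spearman coefficient. State that these are estimates and not powered confirmatory comparisons.

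The cost is one parameter and a few lines of text, and 2.13 allows the analysis plan to be finalised up to database lock. The drug-specific intervals will be wider than a pooled one. The interaction test has limited power, about 64% for a twofold slope difference under the simulation's assumptions. Interpretation should therefore rest on the drug-specific intervals, and a non-significant interaction should not be taken as licence to report the pooled slope alone.

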
In summary, while Anti-Xa measurement is considered the gold standard for monitoring heparins, its predictive value for adequate prophylaxis or therapy in critically ill patients is uncertain. VET and TGA offer broader insights into haemostasis but yield inconsistent results, particularly at low LMWH doses, and remain poorly standardized. Major gaps therefore persist: fixed dosing yields unpredictable Anti-Xa levels; validated therapeutic and prophylactic targets are lacking; the relationship between Anti-Xa and global haemostatic function is unresolved; and the interplay among dosing, Anti-Xa activity, VET, TGA, and patient-specific factors has not been systematically evaluated.

The present protocol addresses these gaps through a prospective observational study in critically ill adults receiving UFH or LMWH. By concurrently measuring Anti-Xa, viscoelastic variables, thrombin generation, and standard laboratory tests, this study aims to determine whether the VET can serve as a reliable surrogate for Anti-Xa monitoring to obtain a broader view of the coagulation system in critically ill patients.

Because Anti-Xa quantifies UFH and LMWH activity in plasma whereas VET reflects whole-blood clot formation influenced by both anticoagulant exposure and the patient’s haemostatic substrate, a strong correlation is not guaranteed in critical illness. The primary objective is therefore pragmatic: to determine whether CT in RVV assay shows a sufficiently stable, monotonic relationship with Anti-Xa to support bedside interpretation as a rapid surrogate for Anti-Xa activity, and to define possible conditions under which this relationship worsens. A stable correlation would support CT-guided interpretation when Anti-Xa results are delayed or logistically constrained; conversely, weak or heterogeneous correlation would question whether VET-based monitoring offers advantages and underscore the need for complementary testing. Associations with clinical outcomes are collected as exploratory signals; the study is not powered to rank assays by clinical endpoints.

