### Handling for repeated measurements

2.14

All inferential analyses involving repeated measurements will apply mixed-effects modelling with patient-level random intercepts. Simple correlation coefficients are presented for descriptive purposes only.

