
Sepsis, multi-organ failure, and endothelial dysfunction alter pharmacokinetics and pharmacodynamics, complicating both drug absorption and elimination. Consequently, Anti-Xa monitoring provides only a concentration-based readout and does not reflect the complex interplay between the procoagulant and anticoagulant pathways. In particular, it neglects the influence of elevated fibrinogen levels due to inflammation, increased platelet activation, and impaired fibrinolytic activity. Similarly, standard laboratory tests such as aPTT and INR are confounded by acute-phase reactants and inflammatory mediators. Additionally, Anti-Xa activity reflects heparin-dependent inhibition of a fixed amount of exogenous factor Xa and is therefore largely independent of endogenous factor X levels. In contrast, CT-RVV in whole blood may be influenced by variations in coagulation factor concentrations, including factors V and X. Such variability is considered part of the biological context of critical illness and is not treated as methodological noise but as a potential modifier of assay concordance. As a result, neither Anti-Xa nor conventional coagulation tests adequately capture the dynamic risk of bleeding and thrombosis in critically ill patients.

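### The random-intercept model protects the primary slope interval and the interaction tests only if patients share one CT–Anti-Xa slope; patient-clustered standard errors would remove that condition

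*Protocol article*

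**What the plan says.** Section 2.13.1 (Primary analysis) specifies a linear mixed-effects model with a patient random intercept and a fixed effect for drug type. It states that this approach "avoids inflation of type I error due to non-independence of repeated observations". On the result it says: "Results will be reported as regression slope estimates (per 0.1 IU/mL increase in Anti-Xa activity) with 95% confidence intervals". Bootstrap intervals are named in that section only for the descriptive Spearman coefficients.

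Section 2.14 makes the structure general: "All inferential analyses involving repeated measurements will apply mixed-effects modelling with patient-level random intercepts". Section 2.13.2 applies it to effect modification, where "potential effect modifiers will be analysed within the mixed-effects framework using interaction terms". The modifiers listed there are sepsis, antithrombin, renal function (creatinine, eGFR) and inflammatory markers (CRP, fibrinogen, albumin).

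The document treats variation in the relation as part of the question. Section 2.13.2 says: "These analyses aim to identify conditions under which CT-RVV and Anti-Xa activity diverge". The Introduction says that "weak or heterogeneous correlation would question whether VET-based monitoring offers advantages". The Discussion says that variation in coagulation factors, among them V and X, "is not treated as methodological noise but as a potential modifier of assay concordance". Factors V and X do not appear in the assay lists of 2.6 and 2.9 or in Table 1.

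**The concern.** A random intercept lets patients differ in their level of CT. It does not let them differ in how much CT changes per unit of Anti-Xa. If they do differ in that, a patient's two residuals are correlated in a way that depends on the Anti-Xa values, and the random intercept does not describe it. That is still non-independence of repeated observations, the very thing the model is said to deal with.

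An interaction term absorbs only the slope variation due to the modifier in that model. What comes from other modifiers, or from unmeasured factors V and X, stays in the error.

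Two results are at stake: the primary slope could look more precise than it is, and ordinary between-patient variation could be reported as modification by sepsis or another marker.

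**Working it through.** **1. Inputs from the protocol.** 66 patients (30 LMWH, 36 UFH), two samples each, ICC 0.3, r = 0.6, 15% dropout (2.12); two-sided 0.05 (2.13.3). There is no plan figure to reproduce for this point; the nearest is the type I statement, checked in step 3 as the case of equal slopes.

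**2. Why the random intercept is not enough when slopes vary.** Write x for centred Anti-Xa:

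CT_ij = β0 + b0_i + (β1 + b1_i)·x_ij + γ·drug_i + e_ij, with var(b0) = σ0², var(b1) = τ², var(e) = σ², and b0 independent of b1.

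- var(CT_ij) = σ0² + τ²·x_ij² + σ²
- cov(CT_i1, CT_i2) = σ0² + τ²·x_i1·x_i2

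The planned model sets τ² = 0. Example on a standardised scale (assumed): mean slope 0.6, residual SD 0.8, ICC 0.3, so σ0² = 0.3 × 0.64 = 0.192. For a patient 2 SD above the mean Anti-Xa at both samples, the within-patient correlation is:

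- τ = 0: 0.192/0.64 = 0.30
- τ = 0.15 (25% of the mean slope): (0.192 + 0.09)/(0.64 + 0.09) = 0.39
- τ = 0.3 (50%): (0.192 + 0.36)/(0.64 + 0.36) = 0.55
- τ = 0.6 (100%): (0.192 + 1.44)/(0.64 + 1.44) = 0.78

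Patients at the extremes of Anti-Xa have most influence on the slope, and it is their data that the model treats as more informative than they are. A skewed Anti-Xa distribution makes this worse.

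**3. Simulation of the planned model.** Mean slopes are equal in septic and non-septic patients (40% septic, assumed), so every significant sepsis × Anti-Xa term is false. All Anti-Xa distributions and slope SDs are assumptions.

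- Set A: roughly normal Anti-Xa, mean 0.25 or 0.4 IU/mL, between-patient SD 0.10–0.25, within-patient SD 0.05–0.25, 15% of second samples missing.
- Set B: the standardised scale above, Anti-Xa ICC 0.5, either normal or log-normal with log-SD 0.6. Ranges span separate runs with and without 15% missing second samples.

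Each cell gives coverage of the nominal 95% CI / false-interaction rate.

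| Slope SD, % of mean slope | Set A | Set B, normal | Set B, log-normal |
|---|---|---|---|
| 0 | 94–96% / 4–6% | 94–95% / 5–6% | 94–96% / 5–6% |
| 25 | 93–94% / 6–7% | 93–94% / 6.5–7% | 90–92% / 8% |
| 50 | 89–93% / 8–10% | 90–91% / 7–12% | 82–85% / 13–17% |
| 100 | 85–89% / 10–15% | 82–85% / 15–16% | 69–71% / 26–27% |

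With equal slopes the plan's statement is confirmed. Most cells rest on 700–2,000 runs; for a true 95% the simulation error is √(0.95 × 0.05/700) = 0.8 points at 700 runs.

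**4. Seven null modifiers, each tested singly (Set A).** Independent tests at 0.05 give 1 − 0.95⁷ = 0.30 for at least one false modifier. The planned model gives 0.31 with equal slopes, 0.44 at slope SD 50% and 0.62 at 100%. The base of 0.30 is ordinary multiplicity; only the increase belongs to this point.

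**5. Alternatives in the same scenarios.** Patient-clustered standard errors give coverage of 92–95% and false-interaction rates of 5–8% in Set A. The leave-one-patient-out version (CR3) gives 92–95% and 3–8% in Set B. A patient random slope gives 94–96% and 5–7% in Set A.

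**The case against.** The strongest reply is that the premise is not established. No section states that slopes vary at random between patients. The Introduction asks whether the relation is stable enough, and the Abstract hypothesises an interpretable monotonic one. Different factor V, X or fibrinogen levels may simply shift a patient's CT, which a random intercept absorbs, and several named modifiers do enter as interaction terms. The type I sentence can also be read narrowly, as a contrast with treating two samples from one patient as independent. The list of model terms is not exhaustive, the variance estimator is not named, and a separate analysis plan is to be finalised before database lock. With two samples per patient a random slope is weakly identified. The study calls itself mainly hypothesis-generating, and no decision threshold hangs on the interval.

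Much of this stands. A reader might infer that the plan expects patient-specific slopes, so that its primary interval and interaction tests are simply wrong. The documents do not support that: heterogeneity is an open question in them, and they give no slope SD. The largest figures in the table need both strong skew and a slope SD equal to the mean slope. Under a normal slope distribution, about 16% of patients would then have CT shortening as Anti-Xa rises (Φ(−1) = 0.16).

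It does not dispose of the point. The article states both a model structure and an error property, and the property fails under the very heterogeneity that the study sets out to look for. A later plan could name a robust variance, but the sentence in 2.13.1 credits the random intercept alone. The exploratory label covers the modifier analyses, not the interval for the primary slope.

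**Conclusion.** The point holds in conditional form. The planned model is valid if patients share one slope apart from the modifier in the model. If the slope SD is about a quarter of the mean slope, the damage is small: coverage about 92–94%, with 90% in one skewed run, and false interactions about 6–8%. At half the mean slope it is material: coverage about 82–93% and false interactions about 8–14%, with single runs between 7% and 17%. Beyond that it grows, most of all with skewed Anti-Xa. Which case applies cannot be told from the documents. The figures rest on the assumed slope SD, Anti-Xa distribution and share of septic patients, and on the plan's ICC of 0.3 applied to the residuals. The slope estimate itself is not in question, only its stated uncertainty. As the interaction analyses are exploratory, the main gain from a change is a valid primary interval.

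**What to change.** In 2.13.1, 2.13.2 and 2.14:

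- Keep the mean model and the patient random intercept. Base confidence intervals and p-values for the Anti-Xa slope and its interactions on patient-clustered robust standard errors with a small-sample correction (CR2 or CR3).
- Report a model with a patient random slope for Anti-Xa as a sensitivity analysis only, since two samples per patient identify it weakly and its variance may be estimated at zero.
- Reword the type I sentence in 2.13.1 so that it rests on the clustered standard errors, or state that the random intercept alone suffices only under a common slope.

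Cost: a sentence in each section and one option in the R code, settled before database lock; no new data. Intervals widen where slopes vary. As a guide, in Set A the mean standard error under the random-slope model rose from 0.167 to 0.182 (9%) and from 0.184 to 0.192 (4%) at slope SD 50%. With equal slopes it rose from 0.150 to 0.153 (2%) and from 0.149 to 0.151 (1%), so little is lost if the worry proves unfounded.

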### Trial objectives

2.1

*Primary objective:* To assess the association between VET and Anti-Xa in critically ill patients with and without sepsis receiving UFH or LMWH, and to evaluate whether VET can serve as a surrogate for Anti-Xa as the reference assay.

*Secondary objective:* To determine whether VET provides complementary or superior information to Anti-Xa activity for characterizing global haemostatic function, as assessed TGA variables, in critically ill patients with and without sepsis.

*Exploratory objective:* To investigate whether extended VET variables and advanced haemostatic biomarkers provide additional information on anticoagulant effects, to explore dose-exposure-response relationships between drug dose, Anti-Xa, VET, and TGA, to assess the influence of patient-level modifiers, and to generate preliminary signals on the predictive value of laboratory profiles for bleeding and thrombotic complications in critically ill patients with and without sepsis.

Given the observational design and sample size, this study is primarily hypothesis-generating. Clinical events, bleeding and thrombosis, are assessed exploratorily and will be interpreted descriptively without claims of definitive prognostic performance.

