The Anti-Xa level at the time of sampling reflects the plasma concentration of the anticoagulant and allows consideration of individual variations in drug absorption and elimination. Interpretation of Anti-Xa activity will account for concomitant antithrombin levels, as assay results depend on endogenous antithrombin when no supplementation is included in the reagent, and may be influenced by reagent composition and acute-phase proteins, particularly in patients receiving UFH. For example, high catecholamine requirements or microcirculatory disturbances, such as those occurring during sepsis, may impair the absorption of subcutaneously administered drugs, leading to subtherapeutic plasma levels and necessitating dose escalation. Conversely, reduced drug elimination, such as in renal failure, may cause accumulation and supratherapeutic levels. To account for the specific haemostatic alterations seen in sepsis, sepsis-specific scores will be recorded. Additional laboratory analyses will include prothrombin fragments 1 + 2 (PF1 + 2), thrombin generation assay (TGA), plasmin-antiplasmin complexes (PAP), plasminogen activator inhibitor (PAI), tissue factor pathway inhibitor (TFPI), and thrombin-antithrombin complexes (TAT) to detect hypercoagulable states and/or impaired fibrinolytic activity. SLTs will also be performed to improve comparability among the heterogenous ICU population and to enable subgroup analyses. The anticoagulants of interest are LMWH and UFH. VET testing will be performed using the RVV-test for LMWH and UFH. Both groups will additionally undergo measurements via extrinsic (EX) and Russell viper venom with heparinase (RVH) tests. Measurements will be performed in patients with prophylactic, intermediate, and therapeutic anticoagulation targets, allowing comparisons of the correlation and adjustability of individualized anticoagulation across different degrees of anticoagulation intensity. Figure 1 provides an overview of the temporal sequence of measurements and planned analyses in the study.

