### Obtained laboratory and patient data

2.10

Primary outcome

1) Variable: VET CT in the RVV test (UFH/LMWH).Metric: Correlation with Anti-Xa activity (for UFH/LMWH); correlation coefficient (Spearman); multivariable mixed-effects regression to account for repeated measures.Aggregation: Point estimates with 95% CI.The time points are as follows: 4 h after the administration of LMWH (expected peak level) or steady-state sampling during continuous UFH infusion.Clinical relevance: Evaluates whether VET-CT can serve as a surrogate for Anti-Xa and assesses its potential as a surrogate monitoring tool.

Secondary outcomes

1) Variable: VET CT in the RVV test (UFH/LMWH); Anti-Xa activity.Metric: Correlation with TGA variables.Aggregation: Spearman correlation coefficients with 95% CIs and regression coefficients for adjusted analyses.Time point: As the primary outcome.Clinical relevance: Examines whether VET provide complementary or superior information to Anti-Xa activity for characterizing global haemostatic function.

Exploratory outcomes

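### The primary question is whether CT-RVV can serve as a surrogate for Anti-Xa, but the primary inferential result is a slope, which does not show how well CT predicts Anti-Xa

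*Protocol article*

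**What the plan says.** **The question.** The Introduction describes the aim as pragmatic: to find out whether CT in the RVV assay has a "sufficiently stable, monotonic relationship with Anti-Xa to support bedside interpretation as a rapid surrogate for Anti-Xa activity". Section 2.1 (Trial objectives) includes in the primary objective "to evaluate whether VET can serve as a surrogate for Anti-Xa as the reference assay". Section 2.10 states the relevance of the primary outcome as: "Evaluates whether VET-CT can serve as a surrogate for Anti-Xa and assesses its potential as a surrogate monitoring tool". The Discussion again asks whether RVV clotting times can take this role.

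**The analysis.** Section 2.13.1 says that "the primary inferential analysis will be conducted using a linear mixed-effects model including" a random intercept for patient and a fixed effect for anticoagulant type. It continues: "Results will be reported as regression slope estimates (per 0.1 IU/mL increase in Anti-Xa activity) with 95% confidence intervals". Spearman coefficients with bootstrap intervals are added, overall and by drug, but section 2.14 limits their role: "Simple correlation coefficients are presented for descriptive purposes only". Passing–Bablok regression is added too, with this qualification: "These criteria are used for methodological characterization rather than to demonstrate assay equivalence". The section closes by saying that the aim is a stable monotonic relationship and not interchangeability. Section 2.13.2 adds interaction terms to look for conditions in which the two assays diverge.

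**The size.** Section 2.12 uses a two-sided test of correlation at r = 0.669 (LMWH) and r = 0.6 (UFH), with alpha 0.05 and power 0.80. The target is 30 LMWH and 36 UFH patients, each measured twice.

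**The concern.** A slope per 0.1 IU/mL of Anti-Xa describes how the mean CT changes with Anti-Xa. A clinician using CT as a surrogate needs the reverse: given this CT, what is the Anti-Xa, and with what error? That error depends on the scatter around the relationship as well as on its slope. A slope can be well separated from zero while CT says little about Anti-Xa in an individual sample.

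The Introduction asks for a relationship that is sufficient to support bedside interpretation, yet nothing in the article says what is sufficient, and no listed result is on the scale on which sufficiency would be judged. Sections 2.1 and 2.10 speak of a surrogate while section 2.13.1 steps back from interchangeability. A reader of the final report could therefore take evidence of association as evidence of surrogacy.

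**Working it through.** **1. The plan's own figures.** Section 2.12 gives 19 pairs for r = 0.669 and 23 for r = 0.6. For a two-sided test of zero correlation, the Fisher z formula n = ((1.96 + 0.84) / atanh r)² + 3 gives 14.99 and 19.34, so 15 and 20. The stated 19 and 23 are therefore not reproduced by that test. They are on the large side, and a Spearman variance factor of (1 + r²/2), which the article does not name, gives 18 and 23. The later steps do reproduce: design effect 1.3, 2/1.3 = 1.54, then 19/1.54 and 23/1.54, rounded up to 13 and 15 patients. The point here uses only the planning values of r, so the difference does not affect it.

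**2. What CT leaves unexplained at the planning values.** If CT and Anti-Xa are bivariate normal, the fraction of the Anti-Xa SD remaining once CT is known is sqrt(1 − r²), and the fraction of variance is 1 − r².

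| Drug | r | Variance left | SD left |
|---|---|---|---|
| UFH | 0.6 | 1 − 0.360 = 64% | 80% |
| LMWH | 0.669 | 1 − 0.448 = 55% | 74% |

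The LMWH value is a Spearman coefficient. If both are read as Spearman and converted by 2·sin(πr/6), they become 0.618 and 0.686, and the SD left is 79% and 73%. Halving the SD would need r = sqrt(1 − 0.25), about 0.87.

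**3. What a non-zero association guarantees at the target size.** With 1.54 effective observations per patient (the plan's ICC of 0.3) and no dropout, the smallest observed r that excludes zero is t / sqrt(n − 2 + t²):

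| Group | Effective n | Smallest r | SD left |
|---|---|---|---|
| LMWH, 30 patients | 46.2 | 0.29 | 96% |
| UFH, 36 patients | 55.4 | 0.27 | 96% |
| All 66 patients | 101.5 | 0.20 | 98% |

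This approximates the mixed-model slope by a simple correlation. It shows that an interval excluding zero is compatible with almost no gain in predicting Anti-Xa.

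**4. In IU/mL.** The article gives no SD for Anti-Xa. Assuming 0.10 to 0.25 IU/mL, the 95% half-width is 1.96 × SD × sqrt(1 − r²). At r = 0.6 it is 0.16 to 0.39 with CT, against 0.20 to 0.49 without. At r = 0.669 it is 0.15 to 0.36 with CT.

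**5. Whether the trial could estimate this error.** At the target size, Fisher 95% intervals around the planning values are 0.47 to 0.80 (LMWH) and 0.40 to 0.75 (UFH). Through sqrt(1 − r²), the SD left would be placed between 60% and 88% for LMWH and between 66% and 92% for UFH. This is imprecise but informative.

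**6. Whether another planned result supplies it.**
- Spearman coefficients measure rank association, carry no IU/mL error, and are descriptive.
- Passing–Bablok tests slope 1 and intercept 0 between a clotting time and an activity in IU/mL. The units differ, so these criteria cannot be read as agreement, and the plan itself does not use them to show equivalence.
- Interaction terms ask whether the slope changes with sepsis, antithrombin and other modifiers, not how large the prediction error is.
- In section 2.13.3, models of surrogate potential are listed for the additional VET parameters, not for CT-RVV.

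**The case against.** The best defence is that section 2.13.1 defines the primary objective as a stable monotonic relationship, that section 2.1 calls the study primarily hypothesis-generating, and that a separate analysis plan, not shown, may hold prediction limits. The point does not rest on that silence. The article itself names both the surrogate question and the primary inferential result, and the two do not match. The disclaimer in section 2.13.1 conflicts with sections 2.1 and 2.10 and does not settle which reading governs.

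Several stronger readings are tempting and are not supported:
- *That the plan delivers nothing beyond a non-zero slope.* Spearman intervals, Passing–Bablok regression and effect-modification models are also planned. They do not close this gap, but they exist.
- *That P < 0.05 would count as success.* No section says so. The Introduction ties support to a stable correlation and says that a weak or heterogeneous one would count against VET-based monitoring. The values 0.6 and 0.669 are inputs to the power calculation, not acceptance limits.
- *That the Discussion concludes surrogacy.* It poses the question, and describes VET as possibly complementing Anti-Xa without universally replacing it.
- *That a known share of patients would be misclassified.* A median split gives 30% (r = 0.6) and 27% (r = 0.669) on the wrong side, but the median is not a decision limit in this protocol. Errors around the intended target ranges cannot be derived from it.
- *That the heparinase channel is wasted.* Section 2.2 says "Both groups will additionally undergo measurements via extrinsic (EX) and Russell viper venom with heparinase (RVH) tests". No analysis of RVH is named, but the article does not say which channels the additional VET parameters cover, and the analysis plan may do so.

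**Conclusion.** The concern holds in this form: the stated surrogate question and the primary inferential result do not match, and no result listed in the article gives the error in Anti-Xa when only CT-RVV is known. At the planning correlations that error is large: 80% of the Anti-Xa SD remains for UFH and 74% for LMWH (64% and 55% of the variance). These figures assume bivariate normality and that the planning values are true. The IU/mL widths rest on an assumed SD. A reader might infer that the trial cannot answer its primary question. That goes too far, because the planned estimates do inform whether a stable relationship exists. What they leave open is whether the relationship is close enough for CT to stand in for Anti-Xa. The improvement is worthwhile and cheap, and the association analysis need not be replaced.

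**What to change.** 1. Keep the mixed-model slope with its 95% CI as the estimate of association, and state that a non-zero slope alone is association, not surrogacy.
2. Add, separately for LMWH and UFH, a mixed model that predicts Anti-Xa from CT-RVV. Report the 95% prediction interval in IU/mL for a new patient, so that between-patient variance is included, and validate it by leaving out whole patients, not single samples.
3. Fix the acceptable prediction error before database lock, with the clinical reasoning for it, and base any surrogate statement on that comparison.
4. Reconcile the surrogate wording in sections 2.1 and 2.10 with the closing statement of section 2.13.1, so that one primary question remains.
5. Optional and exploratory: classification against the intended Anti-Xa range already mentioned in exploratory outcome 3, and CT-RVH as a covariate. With 30 and 36 patients spread over prophylactic, intermediate and therapeutic targets, classification estimates would be imprecise, and the Introduction notes that validated targets are lacking.

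The cost is wording and modest analysis on data already to be collected, with no new samples. The downside is that a surrogate conclusion becomes harder to reach.
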